#### Data sources

The H2O master dataset will include both primary and secondary data sources. The aforementioned surveys will be compiled to include variables describing organizational contexts and outputs. These data are collected by PFs during visits to practices at three time points: (1) baseline, (2) at the end of the implementation of support strategy, and (3) 6 months post-implementation. Secondary data on performance (e.g., ABCS) and patient-oriented outcomes (e.g., hospitalization, length of stay) is extracted from the EHRs and the HIE. Practice performance, i.e., the number of patients who achieved and provider performance on these measures, will be calculated for each practice (Table 2).

**Table 2 Tab2:** Outcome measures from HIE and/or EHR data

Measure (Source)	Numerator	Denominator*	Exclusion	Data Source
Aspirin (PQRS 204/NQF 0068)	Patients in denominator with documented use of aspirin or other antithrombotic	Patients 18+ years of age with Ischemic Vascular Disease diagnosis, or hospital discharge for acute myocardial infarction, coronary artery bypass graft, or percutaneous coronary interventions	On another anticoagulant, GI bleeding history, aspirin allergy	Health Information Exchange (HIE)
Blood Pressure Management 1 (PQRS 236/NQF 0018)	Patients in denominator whose blood pressure was adequately controlled (< 140/90)	Patients aged 18 through 85 years with a diagnosis of hypertension	End stage renal disease, dialysis, renal transplant, or diagnosis of pregnancy	HIE
Blood Pressure Management 2	Patients in denominator whose blood pressure was adequately controlled (age 18–59 and/or people with diabetes or chronic kidney disease < 140/90; age 60–85 < 150/90)	Patients aged 18 through 85 with a diagnosis of hypertension	Lacking a DM or CKD diagnosis	HIE
Cholesterol Management 1 (PQRS 316)	Patients in the denominator whose risk-stratified fasting LDL is at or below the recommended LDL goal	Patients aged 20 through 79 years of age who had a fasting LDL performed		HIE and chart audits
Cholesterol Management 2	Patients in the denominator who were prescribed the recommended dose of statin based on risk status	Patients aged 20 through 79 years of age who had a fasting LDL performed		HIE and chart audits

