B1: Blood Pressure Management 1 (blood pressure adequately controlled)	Aged 18–85 who had a diagnosis of hypertension	65%	70%	> 95%
B2: Blood Pressure Management 2 (blood pressure adequately controlled as per co-morbidity-adjusted targets)	Aged 18–85 who had a diagnosis of hypertension	65%	70%	> 95%
C1: Cholesterol Management 1:** (fasting LDL test AND ≤ LDL goal)	Aged 20–79	15%	25%	> 95%
C2: Cholesterol Management 2:** (fasting LDL test AND prescribed statin if indicated)	Aged 20–79	15%	25%	> 95%
S: Smoking cessation support (screening about tobacco AND received cessation counseling if tobacco user)	Aged 18 years and older	60%	70%	> 95%

^a^Estimates for the baseline percentages for aspirin use, blood pressure management, and smoking cessation support are based on Oklahoma Foundation for Medical Quality (OFMQ) primary care practice initiatives in the state of Oklahoma

^**^The C1 and C2 measures were calculated as the product of the probability of having a fasting LDL test (estimated to be 0.3) multiplied by the probability of having an LDL measure below the target (estimated to be 0.50) or being prescribed a statin if indicated (estimated to be 0.5) conditional on having a fasting LDL test

*Abbreviation*: *LDL* low-density lipoprotein

Practices drop out of QI projects when there is a significant disruption in the practice’s internal (e.g., significant clinician or staff turnover, new EHR) or external (e.g., new ownership) environment. On average, we have experienced a drop-out rate of about 5% during a 6-month initiative from previous experience. We therefore estimated a 10% drop-out rate in this 1-year project. Among the 263 recruited practices, we expect to retain at least 234 practices for the entire duration of the 3-year evaluation program.

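### The exclusion listed for Blood Pressure Management 2 in Table 2 contradicts that row's own numerator and the B2 cohort in Table 3

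*Protocol article*

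**What the plan says.** The B2 row of Table 2 (protocol article, Data sources) makes three statements about who is measured and how:

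- Denominator: "Patients aged 18 through 85 with a diagnosis of hypertension".
- Numerator, the control criterion: "age 18–59 and/or people with diabetes or chronic kidney disease < 140/90; age 60–85 < 150/90".
- Exclusion: "Lacking a DM or CKD diagnosis".

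The B1 row above it uses one limit, < 140/90, for everyone in its denominator.

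Table 3 (Power analysis and effect sizes) describes B2 as "blood pressure adequately controlled as per co-morbidity-adjusted targets". Its cohort column covers hypertensive patients aged 18–85 with no restriction to DM or CKD. The planning figures are 65% before and 70% after the intervention, with power above 95%.

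Nothing else in the article explains or corrects the exclusion.

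**The concern.** The numerator sets a limit for two kinds of patient that the exclusion then takes out of the denominator: those aged 60–85 without DM or CKD, and those aged 18–59 without DM or CKD. One cell of the row cancels part of the next, and the population that remains is not the one in Table 3.

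Table 2 is where the article says how practice performance is calculated, and the Evaluation design section foresees code written to abstract these data from the health information exchange. A query that follows the row literally returns a single-limit measure in a DM/CKD subgroup under the B2 label. ABCS attainment is also the patient-level outcome of the logistic models in the Analytic plan and the content of the monthly reports to practices. A wrong B2 denominator could therefore reach both the evaluation and the feedback. B2 is one of the six endpoints for which Table 3 states power.

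**Working it through.** **1. The plan's own figure.** Table 3's power of > 95% for B2 cannot be reproduced exactly, because the article does not give the number of patients simulated per practice and period (m), and Fig. 4 with the wave spacing is not shown. A linear Hussey–Hughes approximation shows whether it is plausible.

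- From the article: 263 practices, 11 time points, 4 waves, effect ramp 0.25, 0.5, 0.75, 1.0, a further 6-month delay for half the practices, within-practice correlation 0.10, two-sided alpha 0.05.
- Assumed: equal waves, one period before wave 1 starts, and waves 3 or 6 months apart.
- Mean proportion (0.65 + 0.70)/2 = 0.675; total variance 0.675 × 0.325 = 0.2194.
- Between-practice variance 0.10 × 0.2194 = 0.0219; variance of a practice-period mean within practice 0.90 × 0.2194/m = 0.1974/m.
- Power = Φ(0.05/SE − 1.96), with SE the generalised least squares standard error of the intervention effect, adjusted for period.

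| Wave spacing (assumed) | m = 5 | m = 10 | m = 20 |
|---|---|---|---|
| 3 months | 0.538 | 0.808 | 0.976 |
| 6 months | 0.785 | 0.962 | 0.999 |

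The stated power is plausible with roughly 10 to 20 eligible patients per practice and 3-month period. It is stated for Table 3's cohort, all hypertensive patients aged 18–85.

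**2. Whom each limit covers.** The first limit takes everyone aged 18–59 and everyone with DM or CKD at any age. The second is left with patients aged 60–85 who have neither. The wording sets no explicit order for a patient aged 60–85 with DM or CKD, who fits both descriptions. Giving the co-morbidity priority is the only reading in which the DM/CKD words do any work, since all those aged 18–59 are already covered by age. It also agrees with Table 3's description.

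**3. Enumeration.** Ages 18 to 85 are 68 single years (42 from 18 to 59, 26 from 60 to 85). With DM yes/no and CKD yes/no there are 68 × 2 × 2 = 272 cells. The exclusion can mean lacking both conditions or lacking at least one, so both were tried.

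| Group | Cells | Limit | Left if lacking both is excluded | Left if lacking either is excluded |
|---|---|---|---|---|
| 18–59, neither | 42 | < 140/90 | 0 | 0 |
| 18–59, DM and/or CKD | 126 | < 140/90 | 126 | 42 |
| 60–85, neither | 26 | < 150/90 | 0 | 0 |
| 60–85, DM and/or CKD | 78 | < 140/90 | 78 | 26 |
| Total | 272 | 246 at < 140/90, 26 at < 150/90 | 204, all at < 140/90 | 68, all at < 140/90 |

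Under either reading no cell keeps the second limit. The cells are combinations, not patients, so they show which groups vanish and not how large they are.

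**4. Table 2 against Table 3.** After the exclusion every remaining patient has DM or CKD and faces one limit, so nothing is adjusted for co-morbidity. Table 3's cohort has no such restriction. The two tables describe different populations and different criteria under one name.

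**The case against.** The best defence is that no one would apply a cell that cancels half of its neighbour. The numerator and Table 3 agree on the intent, and the phrase reads naturally as a qualifier of the age 60–85 clause that landed in the wrong column. That may well be what happened, but the article does not say so. It explains the error without removing it. It does bear on the remedy: the wording may need to be moved rather than struck out.

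It is also fair that only one of two blood pressure measures is affected; B1, the one tied to a named standard measure, is untouched.

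A reader might infer more than the documents support:

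- *That B2 is underpowered.* No loss can be shown. Neither the simulated number of patients nor the DM/CKD share is given, and the article states that analysing all eligible active patients will give more power than the simulations did.
- *That the identical 65% to 70% for B1 and B2 is itself an error.* In one cohort B2 attainment cannot be below B1's, because its limit is never stricter. Equality remains possible, though, and these are round planning values. Nothing in the article shows that the difference exceeds the rounding.
- *That B2 should carry B1's exclusions* ("End stage renal disease, dialysis, renal transplant, or diagnosis of pregnancy"). B2 cites no standard measure, and the article plans no comparison of B1 with B2. Such detail is commonly left to the full specification.
- *That B2 simply becomes B1.* Only the limit coincides; the populations and the listed exclusions differ.

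**Conclusion.** The contradiction is real. It lies within the B2 row of Table 2 and between that row and Table 3. Taken literally, the exclusion leaves no patient under the age 60–85 limit and drops every hypertensive patient with neither DM nor CKD at any age from 18 to 85. What remains is B1's limit applied to a DM/CKD subgroup, to which Table 3's percentages and power do not refer.

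The result on the second limit rests on one assumption, that DM or CKD takes priority over age where both descriptions fit. Without it, the exclusion would still remove patients aged 18–59 whom the numerator covers and would still conflict with Table 3's cohort. The share of patients affected cannot be derived from the article. Which blood pressure limit is appropriate is not judged here.

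This is an inconsistency of definition in one of six powered endpoints. It should be settled before B2 is extracted. It is not evidence that the design or the power calculation is wrong for Table 3's own cohort.

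**What to change.** Reconcile the B2 row of Table 2 with Table 3 before the query is coded; if code already exists, check which population it extracts. Two routes are open, and the sponsor should say which was meant:

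1. *Full hypertensive cohort.* Remove the phrase as a denominator exclusion. If it was meant to qualify the age 60–85 clause, move it to the numerator. State explicitly which patients each limit covers, including those aged 60–85 with DM or CKD. The denominator is then Table 3's cohort, and this point requires no change to Table 3.
2. *DM/CKD-only measure.* Rename B2, reduce the numerator to what applies in that subgroup, and change the Table 3 cohort, percentages and power to match.

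The first route costs an edit to one table row and the matching query logic, with no new data collection. The second also needs planning figures for the subgroup, which the article does not give, and a new power calculation.

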#### Power analysis and effect sizes

A series of simulation studies were performed to investigate power of the planned evaluation study [41]. A logistic regression model was used to randomly generate data corresponding to the assumed percentage of patients satisfying each ABCS criterion prior to and after the implementation support period as specified in Table 3. The model was specified according to the mean model introduced by Hussey and Hughes [42] and included a random effect corresponding to practice (the unit of randomization), a fixed implementation support effect where the implementation support covariate was modeled using a fractional covariate of (0.25, 0.5, 0.75, and 1.0) for the 3, 6, 9 and 12-month post-initiation practice performance measures to account for an implementation support strategy that is not fully effective until the 12-month time point following initiation. Note that for half of the practices, the fractional covariate is delayed by an additional 6 months relative to the Series implementation scheme given that one pair of targets (blood pressure/smoking or aspirin/cholesterol) is delayed by 6 months in each practice. The model also included a random error term. The correlation among measures made on patients from the same practice was assumed to be 0.10 or less [43]. After the data were generated, Generalized Estimating Equations (GEE) methodology was used to fit a logistic regression model to test the significance of the implementation support strategy effect. The percentage of simulated data sets that resulted in a significant intervention effect was recorded as the power of the specified study design. The power analysis assumes a 2-sided 0.05 alpha level. For each ABCS endpoint, 500 simulated data sets were generated. Estimated power is summarized for each target in Table 3. The power of the implemented analyses will be higher than that from the simulation studies, given that all active patients in the targeted clinical population for a particular ABCS criterion during a 3-month period will be analyzed per practice unit.

**Table 3 Tab3:** Summary of the assumed intervention effect sizes and power

Endpoint	Patient Cohort Characteristics (defining cohort eligible for intervention)	Baseline^a^ Percentage	Post-intervention Percentage	Power
A: Aspirin (aspirin or other antithrombotic prescribed)	Aged 18 years and older with ischemic vascular disease without a contraindication to aspirin	60%	70%	> 95%

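### Tables 2 and 3 define the statin measure (C2) differently: read literally, Table 2 scores a tested patient with no statin indication as a failure, while Table 3 plans on a measure that does not

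*Protocol article*

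**What the plan says.** C2 is defined twice in the protocol article.

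- **Data sources, Table 2.** The numerator is "Patients in the denominator who were prescribed the recommended dose of statin based on risk status". The denominator is "Patients aged 20 through 79 years of age who had a fasting LDL performed". The exclusion cell of this row is blank.
- **Power analysis and effect sizes, Table 3.** The endpoint is "fasting LDL test AND prescribed statin if indicated", in a cohort described only as aged 20 to 79. The rates are 15% at baseline and 25% after the intervention, with power above 95%. The footnote builds the 15% from a testing probability of 0.3 and the probability of "being prescribed a statin if indicated (estimated to be 0.5) conditional on having a fasting LDL test".

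Neither section says how a tested patient with no statin indication is scored, and neither gives the share of tested patients who have one. The Analytic plan needs a yes/no result per patient for each ABCS criterion, so the analysis must settle this.

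**The concern.** A tested adult for whom no statin is recommended has not been prescribed one. Under the words of Table 2 that patient is in the denominator and cannot enter the numerator. Under Table 3 the same patient either satisfies the condition or falls outside it.

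If Table 2 is coded as written, three things follow. The C2 rate cannot exceed the indicated share of tested patients. It can fall when a practice tests more low-risk adults, even if treatment of indicated patients improves. And the monthly feedback described under Performance feedback could show a practice's correct non-prescribing as failure. The planning figures in Table 3 would also describe a different measure from the one extracted.

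**Working it through.** **Inputs.** From the Table 3 footnote: testing probability 0.3; statin if indicated, given a test, 0.5. From Table 3: 15%, 25%, power above 95%. Assumed, because the documents do not give it: q, the share of tested patients with an indication. Also assumed: the footnote's 0.5 is t, the share of indicated patients who are treated.

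**1. The plan's own figure.** 0.3 × 0.5 = 0.15, which reproduces the 15% baseline. It is a share of all adults aged 20 to 79. On Table 2's denominator (tested patients only) the same inputs give 50%, so the two tables also differ in denominator.

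**2. Three ways to score patients without an indication, with t = 0.5.**

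| Scoring | Formula among tested | q = 0.3 | q = 0.4 | q = 0.6 |
|---|---|---|---|---|
| Failure (Table 2 read literally) | q × t | 15% | 20% | 30% |
| Success | 1 − q(1 − t) | 85% | 80% | 70% |
| Outside the measure | t | 50% | 50% | 50% |

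**3. Does the footnote's 0.5 settle the scoring?** Suppose instead that 0.5 is the rate over all tested patients. Scoring as failure then needs q × t = 0.5, and scoring as success needs q(1 − t) = 0.5. Each requires q of at least 0.5. Restricting to indicated patients gives 0.5 for any q, but Table 3's cohort is not restricted in that way. The footnote does not decide it.

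**4. Can 25% be reached on the literal scoring?** On Table 2's denominator the ceiling is q, so 25% needs q ≥ 0.25. On Table 3's denominator the ceiling is testing rate × q:

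- testing stays at 0.3: q ≥ 0.25/0.3 = 0.833
- testing rises to 0.5: q ≥ 0.25/0.5 = 0.5

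**5. Can the rate move the wrong way?** Illustration with assumed counts. Before: 100 tested, 60 indicated, 30 treated, so 30/100 = 30%. After: 150 tested, 70 indicated, 60% of these treated (42), so 42/150 = 28%. Treatment of indicated patients rose from 50% to 60% while literal C2 fell.

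**6. Power.** This was approximated with the Hussey and Hughes generalised least squares variance: 263 practices, 11 periods, four waves by two orders, the fractional covariate, correlation 0.10, two-sided 0.05. Patients per practice-period (m) and wave spacing are not stated; waves one quarter apart are assumed here.

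- 15% to 25%: power 0.97 at m = 3 and 0.998 at m = 5. The stated figure is plausible, though it cannot be reproduced exactly.
- Literal Table 2 scale, with treatment of indicated patients assumed to rise from 50% to 83.3%: q = 0.25 gives 12.5% to 20.8%, with power 0.93 at m = 3 and 0.99 at m = 5. q = 0.5 gives 25% to 41.7%, with power about 1.0 at m = 3.

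**The case against.** The best defence is that Table 2's numerator is tied to risk status. That phrase can be read as doing the work of an indication, so that a patient for whom no statin is recommended has been managed correctly. Table 3 does not fix the scoring either, since it leaves such a patient a success or outside the measure. The article also says, under Resource center, that technical specifications for data collection and reporting are developed separately, and a condensed table need not carry every rule.

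Part of this stands. Failing patients without an indication is one reading of Table 2, not a rule it states, and it would be too strong to say that the two tables prescribe opposite scoring. But the milder reading requires counting as prescribed a patient who was prescribed nothing. Elsewhere Table 2 makes such limits explicit: the smoking row asks for counselling only of identified tobacco users, and the aspirin row confines its denominator to patients with relevant vascular disease or events and lists exclusions. The C2 row does neither. Nor is this just missing detail, because two printed definitions of one outcome disagree.

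A reader might also infer that the 25% target cannot be reached, or that the study lacks power for C2. The documents support neither. The first depends on an unstated q and on testing staying at 0.3, whereas Table 3 counts the LDL test as part of success, so testing may itself rise. On the second, the approximate power stays high in most of the cases tried.

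**Conclusion.** The point holds as a mismatch of definitions. Table 2 followed literally fails tested patients with no indication; Table 3 plans on a measure that does not. With t = 0.5 and q between 0.3 and 0.6, both assumptions, the rate among tested patients is 15% to 30%, 85% to 70%, or 50%, depending only on how those patients are scored. Table 3's 15%, 25% and power above 95% therefore cannot be attached to the measure that Table 2 defines. The ceiling at q and the possible fall in the rate as testing widens belong to the literal reading only. Neither an unreachable target nor a loss of power is established. The matter should be corrected because it determines what is coded, fed back to practices and reported for C2.

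**What to change.** Reconcile Tables 2 and 3 to one C2 numerator and denominator, and state how a patient without an indication is scored, so that such a patient is not a failure. There are two workable forms:

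- restrict the denominator to patients with an indication under the guideline the programme adopts; or
- write the indication as a condition in Table 2's numerator, in the way the smoking row handles tobacco use.

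State at the same time whether the LDL test defines the denominator, as in Table 2, or is part of success, as in Table 3. Use the chosen definition in the analysis and the practice reports, and restate C2's baseline, post-intervention value and power for that population. Any further exclusions should come from the measure specification the programme adopts; the documents give no basis for adding one here.

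The cost is small: an edit to the C2 rows, a risk classification that Table 2's numerator already needs, and a re-run of the C2 simulation. The restricted form has a smaller denominator.

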**Fig. 2 Fig2:**
[figure not shown]
Primary care practices servicing adults in Oklahoma Counties

To recruit these practices, H2O collaborated with professional associations, health systems, payers, the practice-based research network, and the Oklahoma City Area Inter-Tribal Health Board. Incentives for participation included: (1) updates on the new blood pressure and lipid guidelines and ABCS decision aids; (2) in-practice QI support to enhance capacity, (3) assistance with Physician Quality Reporting System requirements for Medicare incentives, (4) credits for MOC Part IV and for Continuing Medical Education, (5) assistance achieving Meaningful Use of EHR certification for enhanced payment, (6) assistance qualifying for the Medicare Transition of Care and Care Coordination payments, and (7) reimbursement for expenses relating to the evaluation component. Moreover, for practices in counties with a County Health Improvement Organization (CHIO), H2O worked with the CHIOs to provide an incentive of $1000 for each participating practice to use for county-wide cardiovascular risk reduction campaigns. A PF contacted interested practices to arrange a kick-off visit to complete the enrollment process.

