Smoking Cessation Support (PQRS 226/NQF 0028)	Patients in denominator who were screened about tobacco use one or more times within 24 months AND who received tobacco cessation counseling intervention if identified as a tobacco user	Patients age 18+ years	Documentation of medical reason(s) for not screening for tobacco use	HIE

^*^Note: Population denominators will be based on active patient—defined as patients who have been seen in the practice within the previous 18 months

*Abbreviations*: *CABG* coronary artery bypass grafting, *CKD* chronic kidney disease, *COPD* chronic obstructive pulmonary disease, *CVA* cerebral vascular accident, *DM* diabetes mellitus, *ED* emergency department, *GI* gastric intestinal, *LDL* low-density lipoprotein, *LOS* length of stay, *MI* myocardial infarction, *PQRS* physician quality reporting system, *NQF* National Quality Forum

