
Logistic regression models will be fit to estimate the effect of the implementation support strategy on the log odds of attaining an ABCS criterion for a given patient. The outcome variable will be a Yes/No indication of attaining an ABCS criterion measured at a patient level. Individual-level data will be analyzed where the nested clustering of patients within practice units, nested within practices and counties will be accounted for using a structured working correlation structure [44].

Poisson regression models, with a log link, will be used to estimate the effect of the implementation support strategy on the incidence rate of patient outcomes, (ED visits, preventable hospitalizations, heart attacks, strokes, GI bleeds, deaths, etc.), where practice unit data are summarized for each 3-month time period. The outcome will be the number of patient events reported among the active adult patients in a practice unit and the offset will be the total number of patient-months of time at risk during the 3-month time period for the practice unit. GEE will be used to account for the correlation among nested practice units within practices within counties and modifying factors will be investigated.(2)Role of internal and external contextual factors and intervention characteristics on the uptake of the implementation support strategy and on practice performance and outcomes.

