## Discussion

### Impact

Oklahoma is among the poorest states in the nation, with a population of 3.85 million, 75.5% of which is white, 7.6% black, 9.0% American Indian, 1.9% Asian, and 9.3% Hispanic [46]. The state has 38 federally recognized American Indian tribes and the majority of its counties are rural. Most rural communities have a large proportion of vulnerable and underserved patients. Relevant to the CVD management goals of H2O, 23.3% of Oklahomans are current smokers, 35.5% have hypertension, 31.1% are physically inactive, and 32.2% are obese [47]. In a 2011 government report, the quality of health care in Oklahoma was rated as “weak,” particularly in chronic disease management [48]. The H2O study, leveraging the establishment of OPHIC, puts forth a coordinated and systematic effort to engage and provide QI resources to practices, in both rural and urban counties, that serve vulnerable populations. Moreover, one of the reasons accounting for poor QI is the lack of infrastructure and appropriate technology. H2O provides technical and financial assistance to help practices with EHR support and connection to a HIE.

Over the course of the study, PFs, ADs, and PFCs support practices assisting them in establishing QI processes, empaneling and risk stratifying their patients, and providing care coordination for those at the highest CVD risk. Such planned care has been demonstrated to reduce hospitalizations, ED visits, utilization, and use of specialists when more active primary care is provided. In addition, practices may have the opportunity to connect to the preventive services registry or implement enhanced referral systems, both available through the HIE. All of these strategies will likely remain with the practice after study completion.

Enrollment in H2O also positions practices to new payment opportunities with OPHIC’s potential capability to negotiate purchasing of advanced primary care services. Of the 263 practices, 195 will have 12 or more months at the end of the study period to implement these advanced primary care services and be prepared for a shared savings payment plan similar to that tested in the multi-payer Comprehensive Primary Care program, or to participate in an Accountable Care Organization.

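### Event rates use a rolling panel of patients seen in the last 18 months, so the rate ratios may partly reflect a changed patient mix

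*Protocol article*

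**What the plan says.** Under Analytic plan, the Poisson models cover "ED visits, preventable hospitalizations, heart attacks, strokes, GI bleeds, deaths, etc", "where practice unit data are summarized for each 3-month time period". The numerator is defined so: "The outcome will be the number of patient events reported among the active adult patients in a practice unit". For the denominator, "the offset will be the total number of patient-months of time at risk during the 3-month time period for the practice unit".

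The term active is defined once, in the footnote to Table 2 (Data sources): "Population denominators will be based on active patient—defined as patients who have been seen in the practice within the previous 18 months". Power analysis and effect sizes describes the panel as taken anew in each period, although it speaks there of the ABCS analyses: "all active patients in the targeted clinical population for a particular ABCS criterion during a 3-month period will be analyzed per practice unit".

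Under Discussion, Impact, project staff are said to assist practices in "empaneling and risk stratifying their patients, and providing care coordination for those at the highest CVD risk". Practice recruitment and enrollment lists among the incentives "assistance qualifying for the Medicare Transition of Care and Care Coordination payments".

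The intention-to-treat statement in the Analytic plan covers practice units. It does not fix which patients belong to a unit.

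**The concern.** Randomized start times make practices comparable before and after start. They keep patients comparable only if the intervention does not affect which patients are counted. Here a patient is counted because of a visit within a moving 18-month window, and after start that window fills with visits made under support. If support brings in patients whose risk differs from that of the existing panel, the event rate moves although nobody's risk has changed.

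This matters because the Logic model section names patient-oriented outcomes as one of the two outcome sets. GI bleeding is also a natural safety outcome for a program that promotes aspirin. A shift in either direction could be read as benefit or as harm.

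**Working it through.** The article gives no event rate, panel size, visit rate or power for these outcomes, so there is no figure to reproduce. The check holds every patient's risk fixed (true rate ratio 1) and asks how far the apparent ratio can move. **All numerical inputs below are assumptions**, except the 18-month window.

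**1. Newcomers with a different risk.** Let the panel grow by a fraction f, with newcomers' event rate k times that of the existing panel. The offset grows with the panel, so

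RR = (1 + f·k) / (1 + f)

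| f | k | RR |
|---|---|---|
| 0.10 | 0.5 | 1.05/1.10 = 0.955 |
| 0.10 | 0.3 | 1.03/1.10 = 0.936 |
| 0.20 | 0.5 | 1.10/1.20 = 0.917 |
| 0.20 | 0.3 | 1.06/1.20 = 0.883 |
| 0.20 | 1 | 1.20/1.20 = 1.000 |
| 0.10 | 2 | 1.20/1.10 = 1.091 |
| 0.20 | 2 | 1.40/1.20 = 1.167 |

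The row with k = 1 shows that growth alone does no harm. The bias comes only from risk mix, and its sign depends on who is added.

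**2. The same effect through the 18-month window.** With v visits per month, let P(active) = 1 − exp(−18v). Take 800 low-risk patients (0.02 events a year, one visit per 24 months) and 200 high-risk patients (0.12 a year, one visit per 6 months).

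- Before: active 800 × 0.528 = 422 and 200 × 0.950 = 190. The rate is (422 × 0.02 + 190 × 0.12)/612 = 0.0510.
- Low-risk visits raised by 50%: active 540 and 190. The rate is (540 × 0.02 + 190 × 0.12)/730 = 0.0460.
- The panel grows by 19% and RR = 0.90.

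If the high-risk patients are instead seldom seen (one visit per 30 months) and their visits double, active high-risk patients go from 90 to 140. The rate goes from 0.0376 to 0.0449, so RR = 1.19.

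**3. Entry through the event itself.** This step applies only if active status is set at or after the event. A lapsed patient who is hospitalized and then seen would become active and the event would count; a lapsed patient without an event would stay out. If a share s of counted events enters this way and support doubles the number of such events, then, ignoring the small added time at risk,

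RR ≈ (1 − s) + 2s = 1 + s

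For s = 0.02 to 0.05, RR is 1.02 to 1.05.

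**4. After the fix.** In a panel fixed before rollout, f = 0 and no event can bring a patient in. RR is then 1.00 when risk is unchanged, provided that events are captured equally well before and after start.

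**The case against.** **The footnote belongs to the ABCS measures.** It hangs on the denominator column of Table 2, and the rows shown there are ABCS measures only. This stands as a caution: the link to event rates rests on the Analytic plan sentence that uses the same term. With no other definition in the article, it is the natural reading.

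**The support is not described as recalling patients.** The list of intervention components contains no outreach to lapsed patients, and empaneling need not mean recall. The help with Transition of Care payments is an enrollment incentive, and nothing ties it to the randomized start. If it was available from enrollment, it would not separate control from support periods. Both points stand. What remains is the statement under Impact that staff help with empaneling, risk stratification and care coordination, which makes an effect on who is seen plausible but not established.

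**Event-led entry depends on timing.** If active status or time at risk begins before the event, step 3 disappears within the period. An article may leave that rule to the full protocol, so its absence is not a fault. The route also cannot apply to deaths, because a patient who has died makes no later visit.

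**An open panel answers a legitimate question**, namely the event rate in the population that a practice currently serves. A closed panel has its own weakness: patients who leave keep adding time while their events may go unrecorded. This is why a fixed panel should accompany the rolling analysis and not replace it.

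A reader might infer that no change in hospitalizations, bleeds or deaths could be attributed to the support. The documents do not support that. The shifts above rest on assumed inputs and would mainly threaten effects of similar size.

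**Conclusion.** The concern holds in a limited form. As written, the risk set for the event rates depends on visits after the randomized start, and practice-level intention to treat does not protect it. The event rate ratios may therefore partly reflect a changed patient mix.

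Size and direction cannot be determined from the documents. With no true effect, newcomers making up 10-20% of the existing panel at 0.3-0.5 times its event rate give about 0.88-0.95; higher-risk newcomers give a ratio above 1; equal-risk newcomers give exactly 1.00. Event-led entry could add about 2-5% for non-fatal events, but only under the timing condition. The conclusion assumes that the footnote's definition governs the event panel and that support changes who is seen. The change is worth making before analysis, but the point does not invalidate the event analyses.

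**What to change.** In the Poisson paragraph of the Analytic plan:

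1. Set active status, and start time at risk, from visits before the first day of each 3-month period. A visit caused by an event in that period then cannot bring the patient in. This does not stop the mix from changing in later periods, so the second step is needed.
2. Pre-specify a companion analysis in a panel fixed before any wave starts: adults active on the first day of month 7, the start of evaluation. Confirm against Fig. 4 that no practice starts earlier. Follow these patients in all periods regardless of later visits, until death or known departure from the practice.
3. State that an effect on events is regarded as secure only if both analyses agree.

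The cost is plan wording and one patient list per practice, built from the EHR and health information exchange (HIE) data already planned, as far as these reach back 18 months before month 7. The downsides are modest. The fixed panel omits later joiners, ages over the study, and may miss events in patients who leave the practice where the HIE does not capture them.
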